**Guide for grade of local reactions**

|                                                                        | Grade 1
mild                                       | Grade 2
moderate                      | Grade 3
severe                | Grade 4
Extreme |
|------------------------------------------------------------------------|---------------------------------------------------------------|--------------------------------------------------|------------------------------------------|----------------------------|
| Pain in injected muscle (including ache) NOT discomfort in skin | No treatment or responds to paracetamol like treatment | Regular paracetamol like treatment needed | Regular strong painkillers needed | Hospitalisation     |
| Itching or irritation in the skin at the site of injection      | No treatment or responds to paracetamol like treatment | Regular paracetamol like treatment needed | Regular strong painkillers needed | Hospitalisation     |

| Local Symptoms – please put in grade, including 0 if no symptoms and measure maximum width of skin lesion in cm |        |       |       |       |       |       |       |       |       |       |       |       |       |       |       |       |
|------------------------------------------------------------------------------------------------------------------------|--------|-------|-------|-------|-------|-------|-------|-------|-------|-------|-------|-------|-------|-------|-------|-------|
|                                                                                                                        | 12 hrs |       | Day 1 |       | Day 2 |       | Day 3 |       | Day 4 |       | Day 5 |       | Day 6 |       | Day 7 |       |
|                                                                                                                        | left   | right | left  | right | left  | right | left  | right | left  | right | left  | right | left  | right | left  | right |
| Pain at injection site                                                                                          |        |       |       |       |       |       |       |       |       |       |       |       |       |       |       |       |
| Itching or irritation at the site                                                                               |        |       |       |       |       |       |       |       |       |       |       |       |       |       |       |       |
| Redness/discolouration (cm)                                                                                     |        |       |       |       |       |       |       |       |       |       |       |       |       |       |       |       |
| Fluid filled blisters (cm)                                                                                      |        |       |       |       |       |       |       |       |       |       |       |       |       |       |       |       |
| Blood filled blisters (cm)                                                                                      |        |       |       |       |       |       |       |       |       |       |       |       |       |       |       |       |
| Hard swelling in skin surface at or close to site (cm)                                                          |        |       |       |       |       |       |       |       |       |       |       |       |       |       |       |       |

Diary

[figure not shown]

|                            |                              |   |   |   |
|----------------------------|------------------------------|---|---|---|
| Date of birth       |                              |   |   |   |
| Trial number        |                              |   |   |   |
| Trial centre        |                              |   |   |   |
| Vaccination number  | 1                            | 2 | 3 | 4 |
|                            | Please circle as appropriate |   |   |   |
| Date of vaccination |                              |   |   |   |

|                         |
|-------------------------|
| Contact details: |
|                         |
|                         |

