## 1.5 End-points

### 1.5.1 Primary

The primary endpoints are immunogenicity and safety as defined below.

The primary immunogenicity parameter will be the presence of CD8/CD4+ T cell responses defined according to internationally agreed criteria for evaluation of IFN $\gamma$  ELISPOT assays (see section 8),

- in response to *env plus* at least one of the *gag, pol, nef* peptide pools
- at weeks 26 or 28

The primary safety parameters will be graded according to appendix 4, and are:

- Grade 3 or above local adverse event (pain, cutaneous reactions including induration)
- Grade 3 or above systemic adverse event (temperature, chills, headache, nausea, vomiting, malaise, and myalgia)
- Grade 3 or above other clinical or laboratory adverse event confirmed at examination or on repeat testing respectively.
- Any event attributable to vaccine leading to discontinuation of the immunisation regimen.

Note of clarification 8th Nov 2006: This will capture all Serious Adverse Events (SAE) as defined by ICH GCP as well as other grade 3 and 4 events that do not meet the criteria of an ICH GCP SAE.

Data on local and systemic events listed above will be solicited with specific questions or using a diary card for a minimum of 7 days following each immunisation. Data on other clinical events and laboratory events will be collected with an open question at each visit and through routine scheduled investigations respectively.

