**2.3.2 Follow-up in the days following immunisation**

A diary card will be given, with instructions and a full verbal explanation, for participants to record local and systemic adverse events for at least 7 days following immunisation, as well as medication taken.

Participants will be observed on the day of immunisation as above. Contact will be maintained by the clinical team, using a method chosen by the participant, as indicated by the evolution of adverse events, up to resolution of solicited local and systemic events. Additional visits may be recommended at the discretion of the clinical and principal investigators, if clinically indicated or in order to clarify observations.

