## **4 Assessments**

### **4.1 Safety assessments**

#### **4.1.1 Local adverse events**

Pain in the muscle injected will be graded by the participant according to the criteria in appendix 4 as mild (1) moderate (2), severe (3) or extreme (4) and recorded in the appropriate case record form or once the participant has left clinic, in the diary card.

Redness will be recorded as the maximum diameter and expressed as a proportion of the arm or thigh circumference and graded on this criteria and the presence of symptoms according to appendix 4. Arm circumference will be measured at screening at the point one third of the way down from the acromio-clavicular joint towards the elbow joint of the non-dominant arm, and thigh circumference half way between the iliac promontory and the patella. Participants will be asked to record the maximum diameter in the diary card, as well as the presence of any itching or other discomfort and any medication taken for relief of symptoms.

Blistering (vesiculation) or ulceration will be graded according to size, depth, time to healing and character of blisters (blood-filled).

The presence of induration (hardened swelling) following intramuscular injection will be considered grade 3 if considered by the clinician to have arisen from a pathological process within the muscle. Induration considered in the judgement of the clinician to result from product leaking into the intradermal or subcutaneous layers will be graded according to the intradermal parameters in the toxicity table (Appendix 4). Soft swelling local to the injection site is not considered induration and should be graded according to the soft swelling parameters in the toxicity table (Appendix 4).

Clinical staff will complete the case record form following each immunisation. Completed case record forms and the diary cards will be sent to the data coordination centres to be recorded on the database. In the event that there are two observations on the same day, those confirmed at a visit will take precedence over diary card observations in the analysis.

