**CUTANEOUS VACCINE REACTIONS**

| Reaction                                                                                                 | Mild                                                                                                                                                                                                        | Moderate                                                                                                                                                                                                                                                                                   | Severe                                                                                                                                                                                                      | Extreme                                    |
|-----------------------------------------------------------------------------------------------------------------|--------------------------------------------------------------------------------------------------------------------------------------------------------------------------------------------------------------------|---------------------------------------------------------------------------------------------------------------------------------------------------------------------------------------------------------------------------------------------------------------------------------------------------|--------------------------------------------------------------------------------------------------------------------------------------------------------------------------------------------------------------------|---------------------------------------------------|

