|                                                                                                                 | Blistering or ulceration at injection site
Fluid filled vesicles or superficial disruption of epithelium covering an area < 1cm                                                                          | Blistering or ulceration at injection site
Fluid filled vesicles or superficial disruption of epithelium, area 1 - 2cm
OR
Blood filled vesicles
OR
Full thickness disruption of epithelium healed within 2 weeks                                                            | Blistering or ulceration at injection site
Full thickness disruption of epithelium not healed within 2 weeks                                                                                             | Necrosis                                          |
| Intramuscular vaccination                                                                                       | Soft swelling – local
Swelling <25% of arm or leg                                                                                                                                                        | Soft swelling – local
Swelling 25-50% of arm or leg                                                                                                                                                                                                                                     | Soft swelling – local
Swelling >50% of arm or leg
Or
Induration/hardened swelling
(when considered by the clinician to be associated with a process arising in the muscle)        |                                                   |

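### The diary card has no row for soft swelling, which section 4.1.1 and Appendix 4 grade separately up to severe, so transient soft swelling may go unrecorded or be entered as hard swelling

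*Protocol*

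**What the plan says.** **Grading.** Protocol section 4.1.1 states: "Soft swelling local to the injection site is not considered induration and should be graded according to the soft swelling parameters in the toxicity table". The scale is in the Appendix 4 table headed "CUTANEOUS VACCINE REACTIONS", under intramuscular vaccination. Mild is below 25% of the limb, moderate is 25 to 50%, and severe is "Swelling >50% of arm or leg". No extreme grade is given.

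**Endpoint.** Section 1.5.1 lists as a primary safety parameter "Grade 3 or above local adverse event (pain, cutaneous reactions including induration)". Soft swelling is not named there. It enters as a cutaneous reaction through the Appendix 4 table or, failing that, as another grade 3 clinical event.

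**Collection.** Section 1.5.1 adds: "Data on local and systemic events listed above will be solicited with specific questions or using a diary card", for at least 7 days. Section 2.3.2 says the card is given "for participants to record local and systemic adverse events for at least 7 days following immunisation".

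**The card.** Appendix 5 has six local rows: pain, itching or irritation, redness, fluid-filled blisters, blood-filled blisters, and "Hard swelling in skin surface at or close to site (cm)". Its guide to local grades covers only pain and itching.

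**The concern.** The protocol takes care to keep soft swelling apart from induration, but the form that participants fill in at home does not make that distinction. A participant with soft swelling on day 2 or 3 has no field for it. The one swelling field describes something else and feeds a scale with different cut-offs.

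What is at stake is the record itself. Section 8.3.2 tabulates solicited local events that start in the first 7 days, by maximum grade and immunisation timepoint. A swelling that was never written down, or was written down as hard, cannot be recovered or reclassified by an analysis plan once it has resolved.

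**Working it through.** The protocol gives no figure to reproduce here. The check compares its sections and then works an illustration of the two scales.

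**Step 1: is there a structured daily field for soft swelling?**

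| Local reaction | Graded in 4.1.1 / Appendix 4 | Row on diary card |
|---|---|---|
| Pain | yes | yes |
| Redness, with irritation | yes | yes (two rows) |
| Blistering | yes | yes (two rows) |
| Induration (hard swelling) | yes | yes |
| Soft swelling | yes, up to severe | no |

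**Step 2: when do staff next see the site?** Section 2.3.1 has an inspection at ten minutes and an observation at one hour. After that, the section 2.6 schedule gives:

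- DNA-C at weeks 0, 4 and 8; next visits at weeks 1, 5 and 9. The gap is 1 − 0 = 5 − 4 = 9 − 8 = 1 week.
- NYVAC-C at weeks 20 and 24; next visits at weeks 22 and 26. The gap is 22 − 20 = 26 − 24 = 2 weeks.

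These gaps are nominal, because the visits have windows. After NYVAC-C the nominal visit falls outside the 7 days that the solicited-event tables cover, so daily information for that week comes from the card or from unscheduled contact.

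**Step 3: would entry in the wrong row change the grade?** Hard swelling attributed to leakage into the dermis is moderate at 1.5 to 3 cm and severe above 3 cm; both grades also require more than 6 days' duration (Appendix 4). Soft swelling is graded by share of limb, with no duration. The documents give no limb sizes and do not say which dimension of the limb the percentage refers to. I assume width over circumference, which is how section 4.1.1 treats redness, with an arm of 25 to 35 cm and a thigh of 50 to 60 cm.

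| Assumed circumference | Moderate from (0.25 × c) | Severe above (0.50 × c) |
|---|---|---|
| 25 cm | 6.25 cm | 12.5 cm |
| 35 cm | 8.75 cm | 17.5 cm |
| 50 cm | 12.5 cm | 25 cm |
| 60 cm | 15 cm | 30 cm |

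Two cases on the arm:

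- Soft swelling of 4 cm for 7 days. Its share is 4/25 = 16% to 4/35 = 11%, which is mild. Read as leakage induration it exceeds both 3 cm and 6 days, which is severe.
- Soft swelling over more than half the arm for 3 days. On its own scale it is severe. Read as leakage induration it fails the duration condition for both moderate and severe.

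So an entry in the wrong row could raise or lower the grade.

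**The case against.** **Other routes exist.** Section 1.5.1 allows specific questions as well as the card, and adds an open question at visits. Adverse events are assessed at every visit from week 0 to week 48. Section 2.3.2 keeps staff in contact while events evolve and permits extra visits. The card invites comments on other symptoms and asks participants to call about grade 3 or 4 symptoms. The case report form is not shown and may have a soft-swelling field. This stands, and it is why the consequence is that events may be missed, not that they are. None of these routes is a structured daily record, however. The comments space sits with the general symptoms, the card offers no soft-swelling grade by which to judge when to call, and a field completed at a visit does not supply the days in between.

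**Investigators assign the grades.** Section 8.2 gives grading to the Clinical Investigators with review by the Operational Sub-Group, section 4.1.1 leaves the origin of induration to clinical judgement, and the card comes with a verbal explanation. A diary entry is therefore not converted to a grade mechanically. This also stands, though once a swelling has resolved the clinician has only the entry to go on.

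**A severe case is hard to overlook.** A swelling over half the limb is the kind most likely to be mentioned by some route. I accept this. The likelier loss is transient mild or moderate swelling, which belongs to the secondary safety endpoints and the solicited-event tables.

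**A reader might infer a bias between arms.** DNAx2 receives two NYVAC-C doses against one in DNAx3, and the visit after NYVAC-C comes later. The documents do not carry this further. The Introduction calls local reactions to NYVAC-based vaccines more marked than those to licensed recombinant products; it makes no comparison with DNA-C. DNA-C goes into both thighs each time, so DNAx3 has 3 × 2 + 1 = 7 injection sites and DNAx2 has 2 × 2 + 2 = 6. Neither direction nor size can be derived.

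**Conclusion.** The mismatch holds: soft swelling has its own scale up to severe and no place on the diary card. Soft swelling that appears and resolves between the one-hour check and the next visit may be lost or entered as hard swelling. The card is used for every immunisation in all 140 participants, but that counts opportunities, not events. The documents give no soft-swelling rate, so the number of affected events is unknown.

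The main consequence is incomplete 7-day solicited local-event tables. An effect on the grade 3 component of the primary safety endpoint is possible but less frequent. The grade-shift examples rest on my assumed limb sizes and on reading the percentage as width over circumference.

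A reader might also infer that the Fisher comparison of the arms is at risk, because one participant can matter when events are few: with 70 per arm, 5 against 0 gives 2 × C(70,5)/C(140,5) = 0.058 and 6 against 0 gives 2 × C(70,6)/C(140,6) = 0.028. The arithmetic is right, but it holds for any rare event and is no forecast for soft swelling. The Introduction reports no grade 3 events in EV01, where 20 volunteers were allocated NYVAC. That number is too small to exclude such events, but it does not support such a scenario. The point is a cheap improvement to data collection, not a threat to the trial's conclusions.

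**What to change.** Reconcile Appendix 5 with section 4.1.1 and Appendix 4:

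1. Add a row to the local part of the diary card for soft swelling at or near the site, in cm, with left and right columns, worded so that a participant can tell it from hard swelling.
2. State how the cm value becomes a percentage of the limb on the existing Appendix 4 scale. That scale does not say which dimension it uses, so a cm row alone would not settle the grade. Section 4.1.1 already has arm circumference measured at screening and defines a thigh measurement, so the denominator needs no new procedure.

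The grading cut-offs stay as they are. The cost is a reprinted card and one database field, with no extra visits or procedures.

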| Vomiting                        | Less than 4 x a day or lasting less than 1 week                        | At least 4 x day or lasting 1 week or more                               | Unable to keep any food or fluids down                         | Hospitalisation     |

- Complete at approximately the same time every day ONLY on days that you are NOT going to clinic
- Fill in temperature and record the grade of other general reactions (use the table above as a guide)
- Add any comments regarding other symptoms
- Record any medication taken including over the counter medicines and anything taken to relieve local reactions
- Record the grade, or size in cm, of local reactions overleaf
- Please contact a member of the trials staff as soon as possible if you experience any symptoms of grade 3 or 4
- When the diary card is complete, please return it to a member of trials staff at your next visit

|                                                               | 12 hrs      | Day 1       | Day 2       | Day 3       | Day 4       | Day 5       | Day 6       | Day 7       |
|---------------------------------------------------------------|-------------|-------------|-------------|-------------|-------------|-------------|-------------|-------------|
| General Symptoms                                       |             |             |             |             |             |             |             |             |
| Date                                                   |             |             |             |             |             |             |             |             |
| Temperature °C                                         |             |             |             |             |             |             |             |             |
| Chills/rigors                                          |             |             |             |             |             |             |             |             |
| Malaise/ tiredness                                     |             |             |             |             |             |             |             |             |
| General muscle aches                                   |             |             |             |             |             |             |             |             |

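### The diary card's only hard-swelling row is limited to the skin surface, so hard swelling in the injected muscle is not prompted between visits

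*Protocol*

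**What the plan says.** The primary safety parameters in Protocol section 1.5.1 include "Grade 3 or above local adverse event (pain, cutaneous reactions including induration". The same section says that data on the listed local and systemic events "will be solicited with specific questions or using a diary card for a minimum of 7 days following each immunisation".

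Section 4.1.1 separates two kinds of induration after intramuscular injection. One "will be considered grade 3 if considered by the clinician to have arisen from a pathological process within the muscle". The other, attributed by the clinician to product leaking into the intradermal or subcutaneous layers, is graded from the intradermal line of Appendix 4, which uses diameter and, above grade 1, duration. The Appendix 4 table of cutaneous vaccine reactions repeats the first rule: hardened swelling sits in the severe column "when considered by the clinician to be associated with a process arising in the muscle", with no diameter or duration attached.

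The diary card in Appendix 5 has six local rows: pain, itching or irritation, redness, fluid-filled blisters, blood-filled blisters, and "Hard swelling in skin surface at or close to site (cm". Its grade guide for local reactions covers pain and itching only. For pain, the guide separates muscle from skin: "Pain in injected muscle (including ache) NOT discomfort in skin". The card also tells participants: "Please contact a member of the trials staff as soon as possible if you experience any symptoms of grade 3 or 4".

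**The concern.** All doses of both products go into muscle (section 2.3.1), yet the hard-swelling row asks about the skin surface. That wording matches the leakage kind of induration and leaves out the kind that section 4.1.1 ties directly to grade 3. Participants have just been told, for pain, to keep muscle and skin apart. One who reads the card literally has no row for a firm lump deep in the thigh or deltoid.

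What is at stake is how completely one component of a primary safety endpoint is collected. Section 8.2 compares the safety proportions between groups with Fisher's exact test. Section 7.7.2 acts on three participants with grade 3 or 4 events attributed to the same product. Timing matters as well: the solicited-event tables in section 8.3.2 count events that begin in the first 7 days and summarise their duration, and sections 5.4.1 and 7.7.1 refer to resolution within 72 hours. An event recalled later without dates is hard to place in any of these.

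**Working it through.** The plan gives no figure to reproduce. The check sets the passages side by side and counts visit intervals.

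**1. Does the card ask for each kind of induration?**

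| Kind of hard swelling | Grading (section 4.1.1, Appendix 4) | Diary row (Appendix 5) |
|---|---|---|
| From leakage into intradermal or subcutaneous layers | By diameter and duration | Yes, the skin-surface row, in cm, left and right |
| From a process in the muscle, as judged by the clinician | Grade 3, no size or duration threshold | None |

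No other row covers it. The only muscle item is pain or ache. Soft swelling, which Appendix 4 also grades, has no row either.

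**2. Would the card lead the participant to call staff?** The instruction to call refers to grade 3 or 4 symptoms. The local grade guide defines grades for pain and itching alone, so the card gives a participant no way of knowing that a painless deep lump could be grade 3.

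**3. Does scheduled contact fill the gap?** Section 2.3.1 has the site inspected at ten minutes and the participant observed for one hour, which is too early for a delayed reaction. Under section 2.3.2, later contact is maintained "as indicated by the evolution of adverse events, up to resolution of solicited local and systemic events", so it follows an event that is already known. No routine enquiry between visits is described.

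**4. How long until the next scheduled visit?** From the schedule in section 2.6, nominal interval = (visit week − immunisation week) × 7 days:

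| Immunisation | Group | Weeks | Interval |
|---|---|---|---|
| DNA-C, week 0 | both | 0 to 1 | 7 days |
| DNA-C, week 4 | both | 4 to 5 | 7 days |
| DNA-C, week 8 | DNAx3 | 8 to 9 | 7 days |
| NYVAC-C, week 20 | DNAx2 | 20 to 22 | 14 days |
| NYVAC-C, week 24 | both | 24 to 26 | 14 days |

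These are nominal values; visit windows of 1 day to 1 week apply.

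**5. What does the card cover in time?** Its printed columns run from 12 hours to Day 7. That spans the nominal interval after DNA-C, but only half of it after NYVAC-C (7 of 14 days).

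Taken together, muscle induration that appears and resolves within one of these intervals is recorded only if the participant volunteers it, enters it in a row that does not describe it, or recalls it at the visit.

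**The case against.** The strongest reply is that the diary is only one of two permitted routes. Section 1.5.1 allows specific questions instead, and under section 4.1.1 clinical staff complete a case record form after each immunisation. That form is not part of the protocol and may well ask about hard swelling of either kind. A question at the next visit can recover an event that has already resolved. The card also has a comments box and asks for other symptoms, it comes with a full verbal explanation, a painful site would be noted in the pain row, and each visit includes an open question. All of this stands. The protocol does not flatly contradict itself, and a reader who inferred that muscle induration can be captured only if still present at the next visit would go too far. What remains is that nothing prompts for it day by day, and that recall gives poorer dates.

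Second, calling such induration automatically grade 3 would also go too far. The grade depends on the clinician's view of its origin, and visit findings override the diary on the same day. A new row would prompt an examination; it would not produce an endpoint event by itself.

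Third, a reader might apply an assumed incidence and an assumed share of early resolution to the planned immunisations (140 participants × 4 = 560) and report a number of missed events. The protocol supplies neither input. The one related figure, no grade 3 events in EV01, where 20 of 24 volunteers were allocated the NYVAC product, is too small a base and does not concern DNA-C. Such a count would also be per immunisation, whereas the Fisher comparison and the rule in section 7.7.2 count participants.

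Fourth, a reader might infer bias between arms, because the nominal intervals sum to 7 + 7 + 7 + 14 = 35 days per DNAx3 participant and 7 + 7 + 14 + 14 = 42 days per DNAx2 participant. This shows that the visit schedules differ. It does not show that events are lost at different rates, which would need product-specific frequency, duration and recall data that the protocol does not contain.

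**Conclusion.** The mismatch is real and minor. The card prompts for the leakage kind of hard swelling and not for the muscle kind, although induration belongs to the primary safety parameter and every injection is intramuscular. Some transient events may be missed, or recorded without usable dates. Neither the number nor any difference between groups can be estimated from the protocol, and no claim of bias in the safety comparison is justified. The immunogenicity endpoint, the sample size and the choice of safety test are unaffected.

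The conclusion assumes that participants read the row as printed and that the verbal explanation does not routinely widen it. If the case record form already has a dated question on deep hard swelling, the remaining gap is smaller still. The change is worth making because it costs little.

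**What to change.** Reword the Appendix 5 row so that it covers any hard swelling at or close to the injection site, whether in the skin or deeper, in cm for left and right. Adjust the table heading, which at present refers to the width of a skin lesion. Add one instruction asking participants to tell staff about any deep hard swelling, so that the clinician, and not the participant, classifies its origin under section 4.1.1. Align the matching case record form field, with onset and resolution dates. The grading rules stay as they are.

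The cost is a minor amendment to the card and form, and a few extra contacts to examine reported lumps. The remedy is partial: the printed columns end at Day 7, so the second week after NYVAC-C would still rest on the instruction to tell staff and on a specific question at the next visit.
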